### Participant and Public Involvement

Survivors of stroke and SCI reviewed and provided input on the various study documents that participants are required to complete during this study. Adjustments were made based on their feedback. A scientific committee composed of clinical stakeholders and researchers has been established and will be involved throughout the entire course of this study.

### Outcomes

#### Clinical Evaluation

The primary objective of this study is to evaluate the clinical benefits of the INTeRAcT program across various domains of the International Classification of Functioning, Disability, and Health (ICF) immediately postintervention and after 9 months of follow-up [106]. Therefore, participants are assessed by a blinded assessor at 3 different time points: T0, T1, and T2 (Figure 1). The assessor remains blinded to treatment allocation to ensure objective outcome evaluation. Participants will be reminded of their upcoming assessment appointments promptly via email or telephone. During data collection, a standardized case report form is completed. This form includes researchers’ notes, demographic and pathology-related data, and the results of the standardized clinical assessments and questionnaires.

##### Data: Clinical Outcome Measures

All outcome measures are collected by a trained, blinded assessor (Figure 4). At baseline (T0), demographic, socioeconomic, and pathology-specific data will be collected. An overview is provided in Multimedia Appendix 2.

The primary outcome of this study is the change in functional independence from baseline to T1, assessed using the FIM and the SCIM.

The FIM-motor [107] evaluates independence in ADLs in individuals with a stroke. It comprises 13 items that assess the level of assistance required for performing ADLs safely and efficiently. These activities include self-care, bladder and bowel management, transfers, and mobility, and are scored on a 7-point ordinal scale ranging from total assistance to complete independence, with a total score between 13 and 91. The FIM has demonstrated acceptable reliability and validity in individuals with stroke [108,109].

The SCIM [110] assesses independence in daily activities in individuals with an SCI. It consists of 19 items divided into 3 subscales: self-care, respiration and sphincter management, and mobility. The total SCIM scores range from 0 to 100, with 0 indicating total assistance and 100 indicating complete independence. The SCIM has been validated and is a reliable measure for this population [111].

Although FIM (stroke) and SCIM (SCI) are condition-specific instruments, both measure the same overarching construct: independence in daily life [112]. To allow pooled analysis across conditions, we analyze percentage change from baseline rather than raw scores, enabling comparison of proportional improvements in functional independence. Both measures will be administered at T0, T1, and T2.

We include several secondary outcome measures representing different levels of the ICF for both stroke and SCI. All secondary outcomes will be administered at T0, T1, and T2.

The EQ-5D-5L [113] measures health-related quality of life across 5 dimensions: mobility, self-care, daily activities, pain or discomfort, and anxiety or depression. Each dimension has 5 response levels: no problems, slight problems, moderate problems, severe problems, and unable to or extreme problems. A weighted health state index is calculated for individuals ranging from less than 0 (a health state perceived as worse than death) to 1 (representing full health), with higher scores indicating better health utility. Additionally, the questionnaire includes a visual analogue scale, where participants rate their perceived health from 0 (worst imaginable health) to 100 (best imaginable health). This scale applies to both stroke and SCI populations [114,115].

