### Sample Size Calculation

The power calculation was performed based on the primary research question: the evaluation of the short-term clinical effect of the INTeRAcT intervention versus usual care at home on independence in daily living, measured using the FIM/SCIM (see the Clinical Evaluation section). As no previous studies have assessed functional independence in both stroke and SCI participants in the chronic phase as a combined group, the calculation was based on a relevant improvement for this mixed population. A total sample size of 90 participants will provide 80% power to detect a 12% significant and relevant difference [93,94] in FIM/SCIM scores between the 2 groups, assuming an SD of 20% [95,96] and a 2-tailed *α* of 0.05. This corresponds to an effect size of 0.6, which is considered a “medium” effect. To account for an expected dropout of 10%, further, 100 participants will be recruited.

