##### Data Analysis

We will perform an intention-to-treat analysis, including all measurements from included participants in this trial, irrespective of whether participants prematurely dropped out. Changes from baseline (T0) in FIM and SCIM scores between the experimental and control groups will be compared using a multivariate linear model with an unstructured covariance matrix, including time and treatment as main effects and a time-by-treatment interaction. The stratification variables “experience using advanced rehabilitation technology” and “pathology” will be included as fixed factors. A sensitivity analysis based on multiple imputation will be conducted if substantial missing data (>5% [133]) are present, to assess the robustness of the results under realistic deviations from the missing-at-random assumption [133]. In addition, the analysis will be repeated while correcting for participant characteristics such as age, time poststroke or SCI, and stroke or SCI severity (FIM or SCIM). The same process will be used for the secondary and stroke-specific outcome measures. As secondary outcomes will be interpreted as exploratory, no formal multiplicity correction will be applied. Additionally, exploratory subgroup analyses will be considered based on pathology.

Descriptive statistics will be used to characterize usual care by group and over time based on the prospectively collected FITT-principles based therapy diaries, ensuring transparent reporting of the therapy that will be received during follow-up. In addition, descriptive statistics will be used to quantify, for the intervention group, the proportion of the 90-hour program corresponding to TOT.

The Leuven Biostatistics and Statistical Bioinformatics Center provided statistical support during this trial’s design and provides ongoing statistical support during this trial.

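### Percentage change from baseline does not put FIM-motor and SCIM on a common footing for the pooled primary outcome, and the scale of the 12% and 20% in the sample size is not stated

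*Protocol article*

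**What the plan says.** Three sections of the Protocol article bear on the scale of the primary outcome.

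- **Data: Clinical Outcome Measures.** The outcome is defined as follows: "The primary outcome of this study is the change in functional independence from baseline to T1, assessed using the FIM and the SCIM". FIM-motor is described "with a total score between 13 and 91", and for the other instrument "The total SCIM scores range from 0 to 100, with 0 indicating total assistance and 100 indicating complete independence". To pool the two conditions, the section says "we analyze percentage change from baseline rather than raw scores, enabling comparison of proportional improvements in functional independence".
- **Data Analysis (Clinical Evaluation).** "Changes from baseline (T0) in FIM and SCIM scores between the experimental and control groups will be compared using a multivariate linear model". Percentage is not mentioned here. Pathology and earlier technology experience enter as fixed factors. Baseline FIM or SCIM severity enters only when the analysis is repeated with further covariates.
- **Sample Size Calculation.** 90 participants give "80% power to detect a 12% significant and relevant difference [93,94] in FIM/SCIM scores between the 2 groups", with an SD of 20%. The section does not say what the 12% and the 20% are percentages of.

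Participant Selection and Recruitment caps entry at 85% independence on the FIM or SCIM and states no lower limit. The article gives neither a baseline distribution nor the expected split between stroke and SCI.

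**The concern.** Percentage change is comparable across two instruments only if zero means the same on both. FIM-motor scores 13 for total assistance where SCIM scores 0. The 13 points sit in the FIM denominator without representing any independence, so they shrink every FIM percentage relative to the SCIM percentage for an equivalent gain. The choice made to allow pooling therefore does not achieve it.

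A second effect operates within each instrument. The percentage falls mechanically as baseline rises, so the size and the variance of the outcome both depend on where a participant starts.

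What is at stake is the meaning of the headline estimate. It becomes an average of gains weighted by scale origin and by the inverse of baseline score. Because the sample size section does not name its scale, a reader also cannot tell which effect the trial was designed to detect.

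**Working it through.** **1. The plan's own sample size.** Inputs from Sample Size Calculation: difference 12, SD 20, two-sided alpha 0.05, power 80%, dropout 10%.

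- Standardised effect: 12/20 = 0.6.
- Normal approximation: n per arm = 2 × (1.96 + 0.842)² / 0.6² = 43.6, so 44 per arm (88 in total).
- Two-sample t-test: 44.6, so 45 per arm (90 in total), with power 0.804.
- Dropout: 90 / 0.9 = 100.

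The stated 90 and 100 reproduce.

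**2. Equal gains on the two instruments.** Let f be the baseline as a fraction of the instrument's range. The ranges come from Data: Clinical Outcome Measures.

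- FIM-motor baseline = 13 + 78f; 10% of range = 7.8 points.
- SCIM baseline = 100f; 10% of range = 10 points.
- Percentage change = gain / baseline × 100.

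| Baseline, share of range | FIM-motor | SCIM |
|---|---|---|
| 10% | 7.8/20.8 = 37.5% | 10/10 = 100% |
| 20% | 7.8/28.6 = 27.3% | 10/20 = 50% |
| 40% | 7.8/44.2 = 17.6% | 10/40 = 25% |
| 50% | 7.8/52 = 15% | 10/50 = 20% |
| 60% | 7.8/59.8 = 13.0% | 10/60 = 16.7% |
| 85% | 7.8/79.3 = 9.8% | 10/85 = 11.8% |

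The ratio of SCIM to FIM percentage is (13 + 78f)/(78f) = 1 + 1/(6f). It exceeds 1 at every baseline: 1.20 at 85% of range, 1.33 at 50%, 2.67 at 10%.

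**3. Equal gains within one instrument.** Eight points is 8/20 = 40% from a score of 20 and 8/80 = 10% from a score of 80. At SCIM 0 the percentage is undefined.

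**4. What the 12% could mean.** At mid-range, 12% of baseline is 0.12 × 52 = 6.2 FIM points or 0.12 × 50 = 6 SCIM points. Twelve percent of range is 0.12 × 78 = 9.4 FIM points or 12 SCIM points. The two readings are materially different effects.

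**5. Power under each reading.** The simulation used 45 per arm and a two-sample t-test. Assumptions not in the article: baselines uniform between a chosen lower bound and 85% of range, an SCI share of 20%, 30% or 50%, and scores clipped at the scale ends. With 1,500 runs the simulation error is about √(0.8 × 0.2/1500) = 0.01.

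With 12 and 20 taken as percent of range and gains additive:

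| Lowest baseline, share of range | Power, percentage change | Power, percent of range |
|---|---|---|
| 5% | 0.57–0.63 | 0.78–0.80 |
| 10% | 0.64–0.69 | 0.78–0.80 |
| 20% | 0.69–0.74 | 0.77–0.79 |
| 30% | 0.72–0.75 | 0.77–0.79 |
| 40% | 0.76–0.77 | 0.79–0.80 |
| 60% | 0.74–0.78 | 0.76–0.79 |

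In the same runs the lowest baseline quartile carries 58–63% of the within-arm variance of percentage change when baselines reach down to 10% of range, 42–43% when they reach 40%, and 36% when all lie at 60–85%. An even share would be 25%.

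With 12% and 20% taken as percentage changes and gains proportional to baseline, percentage change keeps power of 0.79–0.82, and percent of range gives 0.76–0.78.

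**The case against.** A reader might infer that the planned power is lost. The article does not support that. The sample size reproduces from its own inputs, and if 12% and 20% are percentage changes from baseline, the calculation is already on the scale of the outcome. A loss needs two further assumptions: inputs in percent of range, and additive gains. Nor can it be shown by raising the SD while holding the difference at 12, because dividing by baseline enlarges both. With baselines from 10% to 85% of range and 30% SCI, the simulated difference is 22.7 and the SD 46.3, in place of 12 and 20.

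A reader might also infer that a few low scorers dominate the result. That depends on a baseline spread the article does not give. Participants live at home, must be able to perform high-dose rehabilitation, and are excluded if they have no voluntary movement against gravity in the upper and lower limbs. Very low scores are therefore less likely, and SCIM 0 is largely theoretical. At 60% of range and above the contrast between instruments is modest.

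Nor do the three sections plainly contradict one another. Change in scores, as worded in Data Analysis, can be read as percentage change, and Sample Size Calculation is ambiguous rather than conflicting.

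There are safeguards. Randomisation is stratified by condition, so scale origin does not bias the comparison of arms. The analysis is repeated with baseline severity, and subgroup analyses by pathology are considered. These would help expose the problem but do not remove it: pathology as a fixed factor shifts the mean level only, and leaves the unequal weighting of the treatment effect and the unequal variance in place.

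All of this stands against the stronger readings. None of it restores the comparability for which percentage change was chosen.

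**Conclusion.** The point holds in a limited form. On the article's own score ranges, percentage change from baseline does not make FIM-motor and SCIM comparable. An equal share-of-range gain is always a larger percentage on SCIM, by a factor of 1.20 at 85% of range, 1.33 at mid-range and 2.67 at 10%. Within an instrument, low baselines count for more. This is arithmetic and needs no assumption beyond treating equal shares of range as equal gains. It affects what the pooled estimate means, not the validity of the randomised comparison.

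The effect on precision is conditional. It runs from a point or two of power when all baselines are high to roughly 20 points when many are very low, if gains are additive and the planning figures are percent of range. It is nil if gains are proportional to baseline and those figures are percentage changes. The article does not allow a choice between these cases, because it gives no baseline distribution and does not say what the 12% and 20% refer to.

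**What to change.** Before any between-group comparison is seen:

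1. Define the primary outcome as the score in percent of instrument range: FIM-motor as (score − 13)/78 × 100, SCIM unchanged.
2. Include the rescaled baseline as a covariate in the primary model, not only in the repeated analysis.
3. State the 12 and the 20 in Sample Size Calculation on the scale actually analysed, and use the same wording there, in Data: Clinical Outcome Measures and in Data Analysis.
4. Keep percentage change from baseline as a supplementary analysis.

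The Results section puts the last visit at July 9, 2025 and describes data analysis as ongoing. If between-group results have already been seen, percentage change should be reported as planned and the rescaled analysis beside it, labelled post hoc.

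No new data are needed. The cost is a documented late amendment to the primary outcome, submitted to the ethics committees as the article requires of amendments. The rescaled outcome also carries its own assumption, that equal shares of two ordinal scales represent comparable independence, and this should be stated openly.

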**Figure 4. F4:**
[figure not shown]
Flowchart for data collection of the INTeRAcT trial. The figure outlines the timing of clinical, health economic, and process evaluations for participants throughout this study. The “halfway clinical trial” section indicates data collection of the interviews with the INTeRAcT therapists. 6MWT: 6-minute walk test; 10MWT: 10-meter walk test; ARAT: Action Research Arm Test; BORG PRE: Borg Rating of Perceived Exertion Scale; COPM: Canadian Occupational Performance Measure; FAC: functional ambulation category; FIM: Functional Independence Measure; FMA: Fugl-Meyer Assessment; FSS: Fatigue Severity Scale; GAS: Goal Attainment Scaling; HE: health economic ; P1-P9: follow-up period 1-9; SCI: spinal cord injury; SCIM: Spinal Cord Independence Measure; SSEQ: Stroke Self-Efficacy Questionnaire.

The Canadian Occupational Performance Measure (COPM) [116] is an evidence-based outcome measure designed to capture a participant’s self-perception of performance in everyday living over time, across 3 areas: self-care, productivity, and leisure. The participant provides a score between 0 and 10 for importance, performance, and satisfaction. An average score for performance and satisfaction is calculated across all relevant items. It can be used in both study populations [117,118]. In this study, the COPM will also be used to assess the participants’ needs and establish the goals for the GAS, as described below.

The GAS [97] is an individualized evaluation method scored on an ordinal 5-point scale, capturing a person’s individual treatment goals and the extent to which they are achieved. Each goal is rated from +2 (much more than expected) to −2 (much less than expected), with 0 representing the expected level of achievement. The baseline level is typically set at −1, and goals can be weighted by the participant according to their importance or difficulty. GAS will be used for both stroke and SCI populations [119].

The Fatigue Severity Scale [120] is a 9-item scale, assessing the perceived severity of fatigue symptoms over the past week in various daily situations. It evaluates how fatigue impacts functioning and is scored on a 7-point scale, ranging from “strongly disagree” to “strongly agree,” with a minimum total score of 9 and a maximum of 63, with a higher score indicating more impact on daily life. It applies to both populations [121,122].

For the stroke population, additional secondary outcome measures were added, representing different levels of the ICF. All these secondary outcomes will be administered at T0, T1, and T2.

The Action Research Arm Test [123,124] is an observational measure to assess upper extremity performance, including coordination, dexterity, and functioning. It consists of 19 items, with task performance rated on a 4-point scale, ranging from 0 “no movement” to 3 “movement performed normally,” resulting in a total score between 0 and 57, with higher scores indicating better upper limb performance.

The Fugl-Meyer Assessment [125,126] assesses motor functioning in the upper and lower limbs in poststroke participants. It includes 50 test items, with a 3-point ordinal scale for each (0: unable, 1: partial, and 2: [near] normal), resulting in a score between 0 and 100, where 0 indicates no motor function, and 66 indicates an intact motor function.

The Functional Ambulation Category [127,128], a 6-point functional walking test that evaluates ambulation ability, determining how much human support a participant requires when walking and whether or not they use a personal assistive device. A score of 0 indicates the participant cannot walk or needs help from 2 or more persons, while a score of 5 indicates the participant can walk independently.

The 6-minute Walk Test [129,130] measures functional walking capacity by assessing the maximum distance (meters) a participant can cover in 6 minutes.

The 10 Meter Walk Test [129,131] assesses functional mobility and gait by measuring the time needed to walk 10 meters at a comfortable, self-selected speed. Walking speed (m/s) is then calculated as the average of 3 trials.

The Stroke Self-Efficacy Questionnaire [132] is a 13-item self-report scale, evaluating individuals’ confidence in performing ADLs. Each item is rated on a 10-point scale, where 0 indicates “not confident at all” and 10 indicates “very confident,” resulting in a total score ranging from 0 to 130.

For a subset of participants in the intervention group, we will measure time on task (TOT), defined as “repetitive active movements performed by the participant, in line with motor learning principles, and directly related to the therapy block and personalized goals.” Using a stopwatch, we will time the active moments for each therapy component once per week, across the 3-week intervention period. Data for TOT and the process evaluation will be observed simultaneously. We will clearly distinguish between TOT and “other time.” The latter includes ADLs (eg, toileting and drinking), transfer time not related to the goals, rest periods, and preparation time. Observers, who are not the treating therapists, will be positioned to avoid interfering with the therapy while maintaining sufficient visibility and audibility. A standardized method and overview for each therapy block have been developed to guide classification and timing.

##### Data Analysis

We will perform an intention-to-treat analysis, including all measurements from included participants in this trial, irrespective of whether participants prematurely dropped out. Changes from baseline (T0) in FIM and SCIM scores between the experimental and control groups will be compared using a multivariate linear model with an unstructured covariance matrix, including time and treatment as main effects and a time-by-treatment interaction. The stratification variables “experience using advanced rehabilitation technology” and “pathology” will be included as fixed factors. A sensitivity analysis based on multiple imputation will be conducted if substantial missing data (>5% [133]) are present, to assess the robustness of the results under realistic deviations from the missing-at-random assumption [133]. In addition, the analysis will be repeated while correcting for participant characteristics such as age, time poststroke or SCI, and stroke or SCI severity (FIM or SCIM). The same process will be used for the secondary and stroke-specific outcome measures. As secondary outcomes will be interpreted as exploratory, no formal multiplicity correction will be applied. Additionally, exploratory subgroup analyses will be considered based on pathology.

Descriptive statistics will be used to characterize usual care by group and over time based on the prospectively collected FITT-principles based therapy diaries, ensuring transparent reporting of the therapy that will be received during follow-up. In addition, descriptive statistics will be used to quantify, for the intervention group, the proportion of the 90-hour program corresponding to TOT.

The Leuven Biostatistics and Statistical Bioinformatics Center provided statistical support during this trial’s design and provides ongoing statistical support during this trial.

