### Randomization and Blinding

To ensure the integrity of this study, the following randomization procedures have been implemented. Participants (n=100) are randomly assigned to 1 of 2 groups: the intervention group, “INTeRAcT” (n=50), or the control group, “usual care” (n=50). To achieve a balanced distribution across conditions and prior rehabilitation technology experience, participants are stratified by condition (stroke or SCI) and prior technology experience. The latter refers to previous participation in outpatient rehabilitation involving advanced technological devices at a frequency of at least 1 to 2 sessions per week for a minimum duration of 3 months. Allocation concealment is ensured using preprepared randomization lists with a block size of 2. As participants enter this study, an independent team member responsible for randomization, who is not involved in participant contact or data collection, assigns each participant to the next concealed allocation. Recruiters and assessors have no access to the allocation lists and are unaware of the randomization sequence or block size. To ensure objectivity and minimize bias, outcome assessments are conducted by an assessor blinded to treatment allocation. Group assignment will be revealed to participants after the first measurement (T0). In exceptional cases, early disclosure may occur due to practical arrangements for participation in the 3-week intervention; however, the assessor will remain blinded. Participants are instructed not to disclose their allocation. Physiotherapists, participants after T0, and researchers involved in follow-up, process evaluation, and economic evaluation cannot be blinded.

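### The primary FIM/SCIM comparison is a change-score test without baseline as a covariate: valid, but less precise than a baseline-adjusted analysis of the same data

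*Protocol article*

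**What the plan says.** The section on clinical outcome measures defines the endpoint: "The primary outcome of this study is the change in functional independence from baseline to T1, assessed using the FIM and the SCIM". So that the two conditions can be pooled, it adds that "we analyze percentage change from baseline rather than raw scores".

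The clinical Data Analysis section names the method: "Changes from baseline (T0) in FIM and SCIM scores between the experimental and control groups will be compared using a multivariate linear model". The covariance between visits is left unstructured. The model is described as "including time and treatment as main effects and a time-by-treatment interaction". Both randomisation factors, technology experience and pathology, "will be included as fixed factors". No other term is listed for this model.

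The FIM or SCIM score appears as a covariate only in the next step, where "the analysis will be repeated while correcting for participant characteristics such as age, time poststroke or SCI, and stroke or SCI severity". Severity is identified there as FIM or SCIM, and the listed items are participant characteristics, so the baseline score is the natural reading. The same process is then applied to the secondary and stroke-specific outcomes.

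Randomisation does not balance the starting score by design: "participants are stratified by condition (stroke or SCI) and prior technology experience".

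**The concern.** Subtracting baseline is not the same as adjusting for it. Unless T0 and T1 are perfectly correlated, people who start low tend to gain more and people who start high tend to gain less, through regression to the mean. Both scales also have a fixed maximum, and percentage change divides by the starting score, which adds to the negative dependence.

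A change-score comparison leaves that dependence in the residual. The standard error is larger than it need be. In any one trial, if the intervention arm happens to start higher, the estimate is pulled down; if it starts lower, the estimate is pulled up.

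What is at stake is precision in the test that decides the trial. The sample size section plans for 80% power with a margin only for 10% dropout, and recruitment has closed at 102. Further precision can now come only from the analysis, and the variable needed was scheduled for every participant at T0.

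**Working it through.** **Inputs from the protocol article.** Sample Size Calculation: difference 12%, SD 20%, two-sided alpha 0.05, 90 participants (45 per arm), 10% dropout, 100 recruited. The article does not say whether the SD is that of the score or of the change.

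**Assumptions.** The T0–T1 correlation ρ is not given, so 0.5 to 0.9 is used. SDs at T0 and T1 are taken as equal.

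**1. The stated sample size.** n per arm = 2(1.960 + 0.842)² × 20² / 12² = 43.6, so 44 per arm or 88 in total. With the t test, power is 79.5% at 44 per arm and 80.4% at 45. The section states that "A total sample size of 90 participants will provide 80% power", which reproduces. Then 90 / 0.9 = 100.

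**2. What the planned model estimates.** If the responses are changes at T1 and T2, baseline is not in the model as a covariate. If they are the scores at T0, T1 and T2, the unrestricted treatment main effect lets the arms differ at T0. The T1 interaction then equals the raw difference in change. A generalised least squares fit to simulated complete data gave 5.587 for both. Either way the test is a change-score contrast.

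**3. Variance.** With score SD σ:
- change score: 2σ²(1 − ρ)
- baseline-adjusted: σ²(1 − ρ²)
- ratio: (1 + ρ)/2

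If the 20% is the SD of change, the adjusted SD is 20√((1 + ρ)/2):

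| ρ | Variance ratio | SD | Power, 45 per arm | n per arm for 80% |
|---|---|---|---|---|
| as planned | 1 | 20 | 80.4% | 44 |
| 0.5 | 0.75 | 17.32 | 90.2% | 33 |
| 0.7 | 0.85 | 18.44 | 86.3% | 38 |
| 0.8 | 0.90 | 18.97 | 84.3% | 40 |
| 0.9 | 0.95 | 19.49 | 82.3% | 42 |

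A simulation of 20,000 trials gave variance ratios of 0.75, 0.91 and 0.96 at ρ = 0.5, 0.8 and 0.9.

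If the 20% is instead the SD of the score, the change SD is 20√(2(1 − ρ)) = 20.0, 15.5, 12.6 and 8.9. Power then goes from 80.4 to 90.2% at 0.5, from 95.3 to 97.6% at 0.7 and from 99.4 to 99.7% at 0.8, and is essentially 100% either way at 0.9. The variance ratio is unchanged.

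**4. Sensitivity to chance imbalance.** The unadjusted estimate moves by −(1 − ρ) per point of baseline difference. With a score SD of 20, one standard error of that difference is 20√(2/45) = 4.2 points. The shift is −2.1, −1.3, −0.8 and −0.4 points at ρ = 0.5, 0.7, 0.8 and 0.9. The simulated slopes were −0.51, −0.20 and −0.10 at 0.5, 0.8 and 0.9; with baseline adjustment they were about 0.

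**5. Percentage change.** Assumed here: baseline mean 55–75 and SD 15–20 before truncation at 85, on a 0–100 scale. At ρ = 0.7, 0.8 and 0.9, adding a linear baseline term cuts the variance by about 17–22, 11–15 and 6–8% if the effect is proportional to baseline. It cuts it by about 22–28, 18–22 and 13–17% if the effect is constant in points.

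**The case against.** The strongest reply is that nothing is invalid. Baseline is not ignored: it is subtracted, and it is the denominator of the percentage change. Over randomisation the test is unbiased and type I error is kept. This stands. A reader might infer from the missing covariate that the primary result would be biased; the documents do not support that.

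Nor are lost precision and exposure to imbalance two separate harms. The variation caused by random imbalance is already inside the unadjusted standard error. They are one cost seen before and after the data.

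A reader might also infer that the plan leaves two competing main results. It does not. The first model leads, the repeat is supplementary, and the baseline-adjusted result is already prespecified. The question is only which of the two should lead.

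The gain may be small. T0 and T1 are three weeks apart in a chronic population, so a high correlation is plausible, and at 0.9 the saving for absolute change is 5%. The upper power figures also need the 20% to be the SD of change. At ρ = 0.9 that would imply a score SD of 20/√0.2 = 44.7, above the limit of 85/2 = 42.5 for a scale starting at 0 with entry capped at 85. That row is therefore formal for absolute change.

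Finally, the analysis plan is not shown and might constrain the arms to a common T0 mean. The listed treatment main effect does not suggest it, and the article states which analysis carries the FIM or SCIM score.

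**Conclusion.** The point holds as a recommendation on efficiency, not as a fault in validity. The article lists the terms of the primary model and places the baseline score in a supplementary repeat, so the less precise of two planned analyses decides the trial.

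For absolute change the saving in variance is 5 to 25% over correlations of 0.9 down to 0.5, equivalent to needing 42 down to 33 per arm instead of 44. For percentage change it can be somewhat larger, depending on the baseline distribution and the form of the effect. These sizes rest on an assumed correlation and equal SDs; the power figures rest also on reading the 20% as the SD of change. The direction does not depend on that reading.

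**What to change.** Make the baseline-adjusted model primary:
- Enter baseline FIM/SCIM on a common scale, for example percent of range, with a baseline-by-time term, beside pathology and technology experience. Allow a pathology-specific slope if FIM and SCIM behave differently. Alternatively, use a constrained longitudinal model with T0 as a response and a common T0 mean.
- Report the version without baseline as the sensitivity analysis. Keep age and time since onset for the repeated analysis.
- If percentage change stays as the response, note that its dependence on baseline runs through 1/baseline, so one linear term removes most but not all of it.
- Do the same for secondary outcomes whose baseline varies between participants. Leave out Goal Attainment Scaling, where the article says baseline is typically set at −1, so the covariate would be nearly constant.

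The cost is a few degrees of freedom and no new data. Timing needs care. The Results section puts the last visit on July 9, 2025, says no analysis preceded finalisation of the protocol, and says analysis is ongoing. The change should be documented and dated before any unblinded comparison; if that point has passed, it should be reported openly as a change to the plan.
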